### Procedures to implement the intervention

The six interventionists (see Table 3) have professionally diverse backgrounds with several years of neonatal unit experience and have been carefully selected by the research team. The SPIBI training was conducted 1 day per week from October 2017 to October 2018, consisting of theoretical lectures, practical intervention-focused days, and at least six home visits to four different preterm-born children for every interventionist, including subsequent supervision. Each home visit was video-recorded and was then analysed and discussed during supervision. The theoretical lectures were given by Swedish and international researchers and clinicians specializing in fine and gross motor skills development, the cognitive development of preterm children, brain development, the NIDCAP, attachment, parental perspectives, early interventions, special education, early intervention for children with autism, parental mental health, play and interaction, speech and communication development, eating development, strengths-based support and long-term consequences of prematurity. The practical and intervention-focused part of the training were carried out by two infant physiotherapists with clinical and research experience with preterm children through the development of the Dutch post-discharge early intervention programme ToP [48, 49, 51, 64], [name] and [name] from Amsterdam Academic Medical Centre in Holland.

**Table 3 Tab3:** Multidisciplinary team of SPIBI

Member of the team	Role in the team
Professor of Special education	PI of research team, main supervisor of PhD student
Neonatologist, professor of neonatology	Research team main medical researcher, facilitator of the project at the NICUs
Pediatric physiotherapist, PhD in physiotherapy	Research team member, supervisor of interventionists concerning motor development and facilitation
Professor emerita of psychology	Research team member, senior advisor of psychology research in neonatal research environment
Psychologist, PhD student	Research team member, coordinator of recruitment, supervisor of interventionists concerning psychological development and attachment
Neonatologist, PhD in neonatology, NIDCAP-trained	Research team member, senior advisor of early intervention in NICU setting
Neonatal nurse, NIDCAP certified	Interventionist, SPIBI-training graduate
Neonatal nurse, physiotherapist, NIDCAP trained	Interventionist, SPIBI-training graduate
Neonatal home-care children nurse	Interventionist, SPIBI-training graduate
Music therapist	Interventionist, SPIBI-training graduate
Psychologist	Interventionist, SPIBI-training graduate
Physiotherapist	Interventionist, SPIBI-training graduate

### Trial design

The SPIBI trial is a two-arm randomized trial with four recruiting sites in Stockholm. The intervention group (IG) receives 10 visits and two telephone calls from a special trained interventionist (see Table 3). The focus of the intervention is providing strengths-based support of the parent-child interaction, sensitizing parents to infant cues, helping the parent to give optimal developmental support to the infant and enhancing the infant’s self-regulating skills. All extremely preterm children in Stockholm are routinely offered an extensive follow-up test programme, and SPIBI participants are subject to additional assessments at 3 months, 12 months, and 24 months corrected age. Additionally, the children’s preschool teachers will be interviewed when they reach 36 months corrected age. Control participants will have an additional meeting with the project coordinator when they are informed that they have been allocated to the control group, in which information will be provided about the discharge process, their child’s behavioural cues and the importance of parent-child interaction at home. The trial began on 1 September 2018, and recruitment is anticipated to end on 31 August 2020 or at a later date when the target 130 is reached. The intervention will continue for 1 year after the last participant has been included.

### Study setting

The study setting will be conducted mainly in the participants’ home environment, except for the first visit, which is intended to occur in the hospital setting before discharge, if applicable.

### Sample size and statistical power

The hospitals in Stockholm treat more than 100 extremely preterm infants every year, but several of them are not residents of Stockholm County, which is a prerequisite for study inclusion. The study team is prepared to recruit 130 participants, 50% of which will be randomized to the SPIBI intervention. The sample size is based on feasibility, and the assumption is that the effect size of the intervention on the primary outcome measure Emotional Availability Scales (EAS) will be moderate, i.e., Cohen’s d = 0.5. This is largely in line with the results of Flierman et al. [50] for the sensitivity scale of the EAS in the previously mentioned Dutch trial. Hence, we aim to recruit 130 participants, which gives us a power of 0.8 given a normal distribution and an alpha value of 0.05.

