### Statistical analysis plan

Data will be analysed using intention to treat analysis for the primary outcome and separate testing with multiplicity adjustments for secondary outcomes. Data will be analysed using SPSS version 25 (IBM, New York) and reported according to the CONSORT statement for RCTs. Descriptive parametric statistics will be presented as percentage for categorical variables and as mean and SD for continuous variables such as age or centiles if the data is skewed. Comparisons between the two groups will be performed with Mann-Whitney U test for independent samples. Subgroups with additional analyses will also be used for detaching outcome differences according to number of home-visits in total, additional medical diagnoses and whether one or two parents participated in the intervention. The level of significance is specified at 0.05. To account for repeated measures, to model within-subject variance, and to handle correlated data of continuous variables a linear mixed model will be used. An interaction term will be introduced in the model to examine heterogeneity effect. For binary and ordinal outcome variables Generalized Estimating Equation (GEE) will be employed. For the main analysis no missing data will be imputed. However, classical multiple imputation methods will be used for an additional sensitivity analysis if any of the included variables has more than 5% missing observations. The GEE is a technique which produces unbiased estimates under the assumption that missing observations will be missing at random. An amended approach of weighted GEE will be employed if missingness is found not to be at random. We will perform residual analysis to assess model assumptions and goodness-of-fit.

Generalized linear modelling will be used for outcome variables that are not repeated to create regression models with distribution of the binary and ordinal dependent variables.

The Bonferroni method will be used to appropriately adjust the overall level of significance for multiple comparisons. Count variables will be analyzed using the Poisson regression model. Qualitative variables from the semi-structured interviews will be analysed for their thematic content. The Pearson chi-square test will be used to detect associations between categorical variables, and the mean and standard deviation will be presented for normally distributed continuous variables.

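### The stated power of 0.8 is attached to 130 recruited participants but holds only if about 128 of them have analysable 12-month EAS data

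*Protocol article*

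**What the plan says.** All references are to the protocol article.

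- **Sample size and statistical power.** The total is put at 130 with equal allocation: "The study team is prepared to recruit 130 participants, 50% of which will be randomized to the SPIBI intervention". The article says that this number rests on feasibility. The effect on the EAS is assumed to be moderate: "will be moderate, i.e., Cohen’s d = 0.5". The conclusion is "Hence, we aim to recruit 130 participants, which gives us a power of 0.8 given a normal distribution and an alpha value of 0.05". No allowance for loss is mentioned.
- **Trial design** and **Randomization.** The total of 130 recurs as the recruitment target and as the number of allocations generated.
- **Recruitment.** Families enter before discharge and may withdraw at any time.
- **Outcome measurements.** The primary outcome is the EAS, used primarily at 12 months corrected age and again at 24 months.
- **Statistical analysis plan.** "Comparisons between the two groups will be performed with Mann-Whitney U test for independent samples". The same section names a linear mixed model for repeated continuous data. On missing data: "For the main analysis no missing data will be imputed". Multiple imputation is a sensitivity analysis, triggered when a variable has more than 5% missing. On alpha: "The level of significance is specified at 0.05".

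**The concern.** The power figure describes a number of analysed participants but is attached to the number recruited. The two coincide only if almost every family provides a codable film about a year after enrolment. The article does not itself expect that: it allows withdrawal and makes a provision for missingness above 5%, whereas the sample size can absorb a loss of only about 1.5%.

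What is at stake is how a null result is read. The Ethics and dissemination section and the Discussion both anticipate non-significant findings. A reader who takes 0.8 at face value would treat such a finding as somewhat stronger evidence against a moderate effect than the design supports.

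**Working it through.** **Inputs.** N = 130, 1:1 (65 per arm), d = 0.5, normal distribution and alpha 0.05, all from the article. Sidedness is not stated. One-sided alpha would give power 0.886 at 65 per arm, so two-sided is the reading that fits the stated 0.8. Loss rates of 5%, 10% and 20% are assumptions, as the article gives none.

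**Step 1: reproduce the stated figure.** For a two-sample t-test, power comes from the noncentral t distribution with noncentrality d × √(n/2) and 2n − 2 degrees of freedom, where n is the number per arm.

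- n = 65: noncentrality 0.5 × √32.5 = 2.85; power 0.808. The normal approximation gives 0.813.

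The stated 0.8 is correct for 130 analysed.

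**Step 2: the smallest number that still gives 0.8.** Solving for n gives 63.77, so 64 per arm (power 0.801); 63 per arm gives 0.795. The requirement is 2 × 64 = 128. The margin is 130 − 128 = 2 participants, and 2/130 = 1.5%.

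**Step 3: the Mann-Whitney test.** Under normality its asymptotic efficiency relative to the t-test is 3/π = 0.955, so its power at n per arm is about the t-test power at 0.955n.

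- n = 65: 0.955 × 65 = 62.07; power 0.789. Simulation with 20,000 replicates gives 0.795.
- For power 0.8: 63.77/0.955 = 66.8, so 67 per arm, 134 in all.

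**Step 4: loss at 130 recruited.** The number per arm becomes 65 × (1 − loss), with loss taken as equal in the two arms. The detectable effect is the d that gives 80% power.

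| Assumed loss | Analysed | Power at d = 0.5, t-test | Power at d = 0.5, Mann-Whitney | Detectable d, t-test | Detectable d, Mann-Whitney |
|---|---|---|---|---|---|
| 0% | 130 | 0.81 | 0.79 | 0.50 | 0.51 |
| 5% | 123.5 | 0.79 | 0.77 | 0.51 | 0.52 |
| 10% | 117 | 0.76 | 0.75 | 0.52 | 0.53 |
| 20% | 104 | 0.71 | 0.69 | 0.55 | 0.57 |

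Simulated Mann-Whitney power agrees: 0.742 at 58 per arm (about 10% loss) and 0.690 at 52 per arm (20% loss).

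**Step 5: which factor matters.** With no loss, moving from the t-test to Mann-Whitney costs 0.808 − 0.789 = 0.019. With the t-test kept, 10% loss costs 0.808 − 0.765 = 0.043 and 20% costs 0.808 − 0.714 = 0.094. Loss to follow-up is the larger factor from 10% upward; at 5% it costs 0.808 − 0.787 = 0.021, about the same as the change of test.

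**The case against.** The strongest reply is that nothing is miscalculated. The figure follows from its own inputs, the article says openly that feasibility set the number, and missing data were considered. All of that is right. A reader might infer an arithmetic error; there is none. What remains is that a correct figure for 130 analysed is stated for 130 recruited.

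A reader might also infer that the trial will certainly miss 80% power. The article gives no loss rate, so it does not support that. At 5% loss the t-test still gives 0.79.

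A third tempting reading makes the Mann-Whitney test the cause. With complete data its power is 0.789, which rounds to the stated 0.8. Nor is it clearly the primary EAS analysis: the EAS is measured at 12 and 24 months, so the linear mixed model could apply to it. Under that model a family filmed only at 24 months would still contribute, so a missing 12-month film need not be a complete loss. That softens the point but does not remove it: a family that withdraws before 12 months contributes no EAS data, and with the EAS listed only at 12 and 24 months there is no baseline score to adjust for.

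Finally, multiple imputation above 5% missing shows that missingness was foreseen. As a sensitivity analysis it does not change the power of the main analysis.

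**Conclusion.** The point holds in a limited form. Power of 0.8 at d = 0.5 requires about 128 participants with analysable 12-month EAS data under a two-sided t-test, or about 134 under Mann-Whitney, while 130 is the number to be recruited and nothing is added for loss. With the t-test the figure tolerates at most two losses over about a year.

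Over the 5 to 10% range, power is about 1 to 5.5 points below 0.8, depending on the test; at 20% it is about 9 to 11 points below. These sizes rest on assumed loss rates, equal loss in the two arms, a normal outcome, two-sided alpha and one EAS observation per participant. Type I error and the effect estimate are not affected. This should be fixed, but it does not undermine the trial.

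**What to change.** Keep N = 130, since feasibility sets it. In the sample size section:

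1. State the expected proportion without a codable 12-month film, with its basis.
2. Name the test or model that is primary for the 12-month EAS.
3. Restate power and detectable effect for analysable participants under that choice.

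If Mann-Whitney is primary, wording could be: *The target is 130 recruited participants, set by feasibility. If 10% have no analysable 12-month EAS (117 analysed), power for d = 0.5 at two-sided alpha 0.05 is about 0.75, and the effect detectable with 80% power is d = 0.53. With 20% loss (104 analysed) these are 0.69 and 0.57.* For a t-test the figures are 0.76 and 0.52, then 0.71 and 0.55. If the mixed model is chosen, its power should be computed for that model.

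The cost is one paragraph and a slightly less favourable power figure. Recruitment and procedures do not change.

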### Participant inclusion and exclusion criteria

Parents of all EPT children residing in Stockholm County who meet the inclusion criteria will be approached by the end of their child’s hospital stay. Inclusion criteria are that the child was born before 28 gestational weeks (GW), is currently in stable medical condition, and is therefore close to hospital discharge from one of the four neonatal units belonging to the Stockholm Region: Karolinska Hospital Huddinge, Karolinska Hospital Solna, Karolinska Neonatal Unit Danderyd and Sachsska Childhood and Youth Hospital. Exclusion criteria are parents who are not able to communicate in Swedish or English, patients not residing in Stockholm County and acute surgery patients who will spend a substantial amount of time in hospitals far from Stockholm.

### Recruitment and randomization

#### Recruitment

The PhD student working with the project spends 8–20 h per week as a project coordinator (see Table 3) visiting the four neonatal units and two medical child wards to identify families eligible for recruitment. The standard procedure for recruitment includes three visits. The first visit takes place during GW 32–36 and aims to provide initial information about the discharge process in general, including the neonatal follow-up programme and the SPIBI project in particular. This initial visit is only implemented if the nurse or neonatologist in charge of the child considers the patient to be medically stable. Two days to three weeks later, a second visit will take place, during which parental questions are answered and the intervention programme as well as the conditions for participating in an RCT are explained in detail. It is stressed that research participation is voluntary and that the family may withdraw from the project at any time with no further consequences. Participating parents are given a three-page information sheet and a consent form to sign, as well as four baseline assessment questionnaires. During the third visit, informed consent and baseline questionnaires are collected, and information about the project is repeated if necessary. The participant is randomized, and if assigned to the control group, a fourth visit is needed to provide information about this circumstance, as well as the fact that the child and parents are now a part of an extended follow-up starting at 3 months corrected age, and at 1 year corrected age, the PhD student will see the family again for assessment and a follow-up interview. If the participant is assigned to the intervention group, the assigned interventionist will visit the family as soon as possible.

#### Randomization

The [name] of Psychology (see Table 3), who is not involved in recruitment, has block randomized 130 participants using an Internet-based random generator (http://www.randomization.com). The instructions given to the random generator are separately stored and the procedure will be cross-checked when all participants have been randomized. All families agreeing to participate in the SPIBI are assigned a serial number 1–130 in chronological order from the date on which they signed the informed consent, and this information is stored in a safe locker separate from the baseline questionnaires.

An overview of the flow chart of the study, including the recruitment process may be found in Fig. 3.

**Fig. 3 Fig3:**
[figure not shown]
Study flow chart of SPIBI

### Evaluation methods

#### Fidelity check

Following each home visit, the interventionist completed a fidelity check of seven questions and one self-evaluation on a scale from 1 to 10 of the interventionist’s faithfulness to the manual during the home visit.

#### Outcome evaluation

The contents of the outcome measures are threefold: parent-child interaction concerning emotional availability, the child’s development and parental mental health.

#### Parental satisfaction

Since the Swedish Preterm Federation has expressed a need for a post-discharge programme and thus stimulated the development of the SPIBI, the views of the participating parents of the benefits and weaknesses of the intervention is of particular importance. All parents will be asked to participate in a semi-structured interview concerning parental satisfaction after the intervention, in addition to rating the intervention with the Client Satisfaction Questionnaire (CSQ-8).

### Outcome measurements

Since the SPIBI is a multi-professional intervention, the outcome is measured across several domains: outcomes concerning emotional availability in the dyadic relation, outcomes measuring child development and outcomes related to parental mental health and parenthood.

The *primary outcome* is the Emotional Availability Scales (EAS) [65], which will be used primarily at 12 months corrected age but then again at 24 months corrected age. The primary coder is blind to group allocation, whereas the second coder, who is used for interrater reliability checks in 20% of the cases, is not. The scale has four parental dimensions (sensitivity, structure, non-intrusiveness, and non-hostility) and two child dimensions (child responsiveness and child involvement). Each subscale has a maximum score of 29 and a direct score of 1–7. It is hypothesized that higher scores will be observed in the intervention group. Previous international studies have shown significant effects of parental sensitivity and structuring as well as child involvement [50], which also seem to be the subscales most indicative of maternal anxiety in the NICU [66].

The *secondary outcome measurements* are listed below. For measuring the cognitive, language, and motor development of the children, the Bayley Scales of Infant and Toddler Development, Third Edition (BSID-III) [67], will be used at 24 months corrected age. Composite scores are standardized to mean (SD) scores of 100 [15], based on age-matched normative data. The secondary hypothesis is that the mean will be higher in the intervention group.

The child’s executive function at 24 and 36 months corrected age will be measured with the Behaviour Rating of Executive Function, Parental Version (BRIEF-P) [68, 69]. All 5 subscales (*inhibit, shift, emotional control, working memory and plan/organize)* will be used, and the hypothesis is that the intervention group will have fewer executive problems reported.

Child’s motor development will be measured by the Alberta Infant Motor Scale (AIMS) [70, 71] at 3 and 12 months corrected age. The range of the AIMS is 0–58 points, with a hypothesis of higher scores for the intervention group.

Parental depression will be measured by Hospital Anxiety and Depression Scale (HADS) [72, 73] at term age and at 12, 24 and 36 months corrected age. On the HADS, the range for the depression subscales is 0–21, and the range for the anxiety subscales is 0–21. It is hypothesized that lower scores will be observed for the parents of the children in the intervention group.

Parental anxiety will be measured by the State-Trait Anxiety Inventory (STAI) [74] at term age and at 12, 24 and 36 months corrected age. Both the state and trait scales have a maximum score of 80 points. It is hypothesized that lower scores will be observed for the parents of the children in the intervention group.

Parental self-efficacy will be measured by the Parental Self-Efficacy Scale (PSE) [75] at term age and at 12, 24 and 36 months corrected age. The PSE has 24 items for children at term age and at 12 and 24 months corrected age, while it has 48 items for children of older ages. All items are rated on a 0–10 scale. It is hypothesized that higher scores will be observed for the intervention group at 12, 24 and 36 months corrected age.

Parental resilience will be measured by the Resilience Scale (RES) [76, 77] at term age and at 12, 24 and 36 months corrected age. The RES is a 25-item scale with a 7-point Likert scale. It is hypothesized that higher scores will be observed in the intervention group.

The *other outcome measurements* are listed below. The Hammersmith Neonatal Neurological Outcome (HNNE) is used at term age as a baseline measurement. Post discharge neurological development will be assessed with the Hammersmith Infant Neurological Examination (HINE) [78–80] at 3 months, 12 months, and 24 months corrected age. It is hypothesized that higher scores will be observed for the intervention group. The HINE can be used for infants 2–24 months of age and has optimal scores as well as cut-off values for future less fortunate motor outcomes. It includes 26 items assessing posture, movements, muscle tone, cranial nerve reflexes and reactions, with a score range of 0–3 for each time, thus yielding a possible sum of 0–78 points.

Children’s motor development will be measured using Peabody Developmental Motor Scales (PDMS) [81] at 12 months corrected age. It is hypothesized that higher scores will be observed for the intervention group. The ranges for each subscale are as follows: stationary, 0–42; locomotion, 0–138; object manipulation, 0–30; grasping, 0–44; and visual-motor integration, 0–113. It is hypothesized that higher scores will be observed for the intervention group.

Children’s neurological development will be measured using the General Movement Assessment (GMA) scale (normal-absent fidgety) at 3 months corrected age [82–84].

Children’s general development will be measured using the Ages and Stages Questionnaire (ASQ-R) [85–87] at 12, 24, and 36 months corrected age. It is hypothesized that the parents of the children in the intervention group will score their children higher. All five subscales (communication, gross motor, fine motor, problem solving, personal-social) will be used, with an overall score ranging from 0 to 300. It is hypothesized that higher scores will be observed for the intervention group.

Children’s strengths and difficulties will be measured using the Strengths and Difficulties Questionnaire (SDQ) [88, 89] at 24 and 36 months corrected age, with the hypothesis that fewer difficulties and more strengths will be scored by parents in the intervention group. The SDQ consists of 25 items on a 3-point scale: 5 items on prosocial behaviour and 20 questions about various difficulties. It is hypothesized that higher scores will be observed for the intervention group for prosocial behaviour and that lower scores will be observed for the intervention group on the problematic subscales.

Child’s autistic symptoms will be measured using the Modified Checklist for Autism in Toddlers (M-CHAT) [90] at 24 months corrected age. The scale ranges from 0 to 20 points, and it is hypothesized that lower scores will be observed for the intervention group.

Infant temperament is measured using the Infant Behaviour Questionnaire (IBQ-R) [91, 92] at 12 months corrected age. The IBQ-R consists of 37 items on a 7-point scale, and it is hypothesized that less problematic behaviour will be observed for the intervention group, i.e., the intervention group will have higher scores on smiling, laughter and soothability subscales and lower scores on the fear and distress to limitations subscales.

Parental satisfaction with the intervention is measured using the Client Satisfaction Questionnaire (CSQ-8) [93] and a semi-structured interview at 12 months corrected age. The CSQ-8 has 8 items and a range of 8–48 points.

Preschool educators’ views of the children’s engagement in preschool is measured using the Child Engagement Questionnaire (CEQ) [94, 95] at 24 and 36 months corrected age. The Swedish version of the CEQ has 29 items rated on a 4-point scale, and the summary score may range from 29 to 116, with higher scores indicating more positive engagement.

Preschool educators’ views of the children’s interaction in preschool will be measured using the Swedish questionnaire Ert Barn Vårt Samspel (EBVS) [94] at 24 and 36 months corrected age. The questionnaire has 36 items rated on a 5-point scale, and the summary score may range from 36 to 180, with higher scores indicating more interactive behaviour.

Preschool educators’ views of the children’s playtime in preschool will be measured using the play time/social time teacher impression scale [96, 97] at 24 and 36 months corrected age. The teacher impression scale has 16 items rated on a 1–5 Likert scale (overall score range: 16–80), with higher scores indicating more social skills and play behaviour. It is hypothesized that higher scores will be observed for the intervention group.

Preschool educators’ views of the children in preschool will be captured using a semi-structured preschool teacher interview at 24 or 36 months corrected age, depending on when the child has entered preschool.

Preschool educators’ views of the children’s level of functioning in preschool were captured with the ICF-CY core sets [94] at 24 and 36 months corrected age. The ICF-CY has 12 items on body functions (rated 0–9) and 22 items (rated 0–9) on activities and participation; higher scores indicate disability or developmental delay. Twenty items covering environmental factors (between + 4 and + 1 for facilitators; 0–9 for barriers) were included to identify possible disability and environmental moderators.

